## Abstract

**Background:**

Stroke can have devastating consequences for an individual’s quality of life. Interventions capable of enhancing response to therapy would be highly valuable to the field of neurological rehabilitation. One approach is to use noninvasive brain stimulation techniques, such as transcranial direct current stimulation, to induce a neuroplastic response. When delivered in combination with rehabilitation exercises, there is some evidence that transcranial direct current stimulation is beneficial. However, responses to stimulation are highly variable. Therefore biomarkers predictive of response to stimulation would be valuable to help select appropriate people for this potentially beneficial treatment.

**Objective:**

The objective of this study is to investigate connectivity of the stimulation target, the ipsilesional motor cortex, as a biomarker predictive of response to anodal transcranial direct current stimulation in people with stroke.

**Methods:**

This study is a double blind, randomized controlled trial (RCT), with two parallel groups. A total of 68 participants with first ever ischemic stroke with motor impairment will undertake a two week (14 session) treatment for upper limb function (Graded Repetitive Arm Supplementary Program; GRASP). Participants will be randomized 2:1 to active:sham treatment groups. Those in the active treatment group will receive anodal transcranial direct current stimulation to the ipsilesional motor cortex at the start of each GRASP session. Those allocated to the sham treatment group will receive sham transcranial direct current stimulation. Behavioural assessments of upper limb function will be performed at baseline, post treatment, 1 month follow-up and 3 months follow-up. Neurophysiological assessments will include magnetic resonance imaging (MRI), electroencephalography (EEG) and transcranial magnetic stimulation (TMS) and will be performed at baseline, post treatment, 1 month follow-up (EEG and TMS only) and 3 months follow-up (EEG and TMS only).

**Results:**

Participants will be recruited between March 2018 and December 2018, with experimental testing concluding in March 2019.

**Conclusions:**

Identifying a biomarker predictive of response to transcranial direct current stimulation would greatly assist clinical utility of this novel treatment approach.

**Trial Registration:**

Australia New Zealand Clinical Trials Registry ACTRN12618000443291; https://www.anzctr.org.au/Trial/Registration/TrialReview.aspx?ACTRN=12618000443291 (Archived by WebCite at http://www.webcitation.org/737QOXXxt)

**Registered Report Identifier:**

RR1-10.2196/10848

## Introduction

Globally, stroke is a leading cause of death and disability. According to the World Health Organization, there were 6.7 million stroke-related deaths in 2012, with 33 million stroke survivors living with persistent disability, requiring long-term care and secondary prevention measures [1]. A stroke affecting the sensorimotor network can lead to behavioral impairments, restricting the capacity to perform various activities of daily living. As a result, many stroke survivors require multidisciplinary rehabilitation to help restore function [2]. Despite lengthy periods of rehabilitation, significant impairments often remain, suggesting there is a need to do more to assist survivors of stroke.

Restitution of upper limb function following stroke is important to improve capacity to undertake activities of daily living and enhance quality of life. Underpinning functional restitution is a process known as neuroplasticity where both structure and function of the surviving brain tissue can change to optimize behavior. Research indicates there may be a time-limited window of enhanced neuroplasticity following stroke [3,4]. This period of enhanced neuroplasticity following stroke has many similarities to those that occur during development where the brain is highly plastic and rapid learning occurs [3]. Delivering rehabilitative therapies during this time may provide an opportunity for a more complete recovery. It is generally thought that this period of enhanced neuroplasticity occurs early after stroke [3,4]. In support of this, behavioral evidence indicates that therapy delivered early after stroke may be more effective than that delivered later [3,5,6]. Furthermore, consensus statements suggest that delayed initiation of rehabilitation is associated with poor outcomes and longer hospital stay [7,8]. However, it should be noted that while early therapeutic intervention may be more effective, recovery long after stroke remains possible. In support of this, there is good evidence indicating that constraint induced movement therapy is capable of improving function months or years after the initial stroke [9-11], suggesting the window for recovery may never really close [3].

One interesting approach to stroke rehabilitation is to attempt to reestablish a period of enhanced neuroplasticity to boost the effects of therapy in people with stroke. The potential for a more complete functional recovery by re-establishing a period of enhanced neuroplasticity was recently shown in an animal model of stroke [12]. In this study, Zeiler et al [12] demonstrated that a second ischemic event reopened a period of heightened response to training, facilitating recovery from the initial stroke. While this approach to facilitate functional recovery may not be appropriate in humans, it does suggest that increased responsiveness to therapy can be achieved by reestablishing a period of enhanced neuroplasticity.

Noninvasive brain stimulation techniques, such as transcranial direct current stimulation (tDCS), are novel approaches that may be able to facilitate neuroplasticity. It is thought that tDCS is capable of altering the level of intrinsic postsynaptic activity depending on the direction of current flow [13,14]. When applied to the primary motor cortex (M1), anodal tDCS increases cortical network excitability, and cathodal tDCS decreases cortical network excitability. Changes in excitability induced by tDCS are thought to be mediated by long-term potentiation and long-term depression-like synaptic plasticity [13,14]. Several studies have demonstrated functional improvements in people with stroke, following plasticity protocols applied to the lesioned M1 [15,16]. However, recent reviews highlight that, at the group level, tDCS does not provide additional benefits to therapy [17]. Upon further investigation, it appears responses can be highly variable among individuals, suggesting this is not a one-size-fits-all treatment. Several factors are known to influence the response to tDCS, including properties of the stimulated brain network, genetics, and endogenous cortisol levels [18,19]. Recently, we demonstrated that a measure of connectivity of the stimulated network was a strong predictor of response to anodal tDCS in healthy adults [20]. Using electroencephalography (EEG), we found that connectivity between electrodes overlying the stimulated M1 and the ipsilateral parietal cortex in the high beta frequency (20-30 Hz) predicted 69% of variability in the neuroplastic response to anodal tDCS using a leave-one-out and predict analysis. Along similar lines, connectivity of the stimulated ipsilesional motor network in alpha frequency (8-13 Hz) was strongly associated with the change in corticospinal excitability following tDCS in people with stroke [21].

Further evidence of the role that functional brain networks may play in modulating response to tDCS is available from other clinical populations. For example, in people with fibromyalgia, connectivity among the thalamus, posterior insula, motor cortex and sensory cortex was a marker of better analgesic response following tDCS applied to M1 [22]. Similarly, responses to tDCS applied to the dorsolateral prefrontal cortex in people in a minimally conscious state were associated with connectivity between the dorsolateral prefrontal cortex and inferior frontal gyrus [23]. It may be that the connectivity of the network targeted by tDCS can be a useful predictor of responsiveness to brain stimulation therapy. Indeed, this may be even more critical following a stroke, where damage as a result of the lesion can interrupt functional connectivity [24].

The primary objective of this study is to determine whether connectivity of the cortical target for tDCS modulates responses to this intervention in people with stroke. The secondary objectives of this study are to determine whether facilitatory tDCS applied to the ipsilesional hemisphere in combination with an upper limb exercise program provides greater behavioral improvement compared with sham stimulation and to determine whether additional neurophysiological characteristics, such as lesion size, cortical excitability, and white matter integrity, modulate the responsiveness to tDCS. We hypothesize that the response to anodal tDCS will be variable; participants who have greater functional connectivity of the ipsilesional motor network will have stronger responses to the stimulation as shown by a greater increase in upper limb function following the intervention period. Outcomes from this study will have important implications for the clinical translation of tDCS in stroke rehabilitation. The ability to select people who will respond to this therapy could substantially improve the clinical translation of this treatment approach.

## Methods

### Study Design

The SPIRIT (Standard Protocol Items: Recommendations for interventional trials) recommendations were referenced when developing this protocol. This protocol has been registered in the Australian and New Zealand Clinical Trials Registry (ACTRN12618000443291). This study is a double blind, randomized controlled trial, with 2 parallel groups. Both outcome assessors and participants will be blind to allocation. Randomization will be performed using a computerized sequence generation by an external researcher. As our primary research aim is to investigate the brain connectivity of participants allocated to the active treatment group, the allocation will be weighted 2:1 toward the active treatment group. A sham treatment group will be used as a comparator to demonstrate the effectiveness of this intervention at the group level and to demonstrate that brain connectivity is not associated with response to sham tDCS.

The study protocol has been approved by the University of South Australia Human Research Ethics Committee (application identification 0000036781; approved May 19, 2017). Recruited participants will provide written informed consent in accordance with the World Medical Association Declaration of Helsinki.

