### Sample Size

Our primary aim is to determine the characteristics of the sensorimotor network at baseline that may predict the responsiveness to anodal tDCS in people with stroke. Therefore, our sample size calculation was based on pilot data of 10 people with stroke where we observed a medium to large effect size (r=0.56) for a correlation between baseline high beta frequency connectivity and change in cortical excitability following anodal tDCS [21]. Using this effect size with alpha set at .05 and power of 95%, we determined a total sample of 47 would be required. However, we will aim to recruit a total sample of 68, given our methodological approach of using unequal group allocation (additional 12%) and the nature of the home-based treatment with a longer follow-up study period (allowing 30% dropout). This will result in 45 participants in the active treatment group and 23 participants in the control group.

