### Statistical Analysis

Normality of data will be confirmed using Shapiro-Wilk normality tests. Where required, data will be normalized using transformations or nonparametric statistics applied. Participants’ demographics and clinical characteristics will be compared between active and sham groups. The effect of the intervention on behavioral and neurophysiological outcome measures will be investigated with a 2 Group (active, sham) × 4 Time Point (Baseline, Postintervention, 1-Month Follow-up, 3-Month Follow-up) repeated measures analysis of variance. Independent variables (Textbox 5) will be correlated with the primary outcome measure for response to anodal tDCS (change in upper limb impairment measured with the UE-FM). Where appropriate, regression models will be generated using those independent variables significantly correlated with change in upper limb impairment to identify a combination of measures associated with response to anodal tDCS. Any regression models generated will be compared using the Bayesian information criteria [45]. Where appropriate, the predictive capacity of the generated model will be investigated using a leave-one-out cross-validation. This cross-validation will be performed on participants allocated to both active and sham treatment groups to demonstrate that the predictive model is specific to the stimulation group. Statistical testing will be performed using SPSS (IBM Co, version 24.0) and significance level will be *P* ≤.05.

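### Whether connectivity modulates the response to tDCS is to be judged from an association in the active arm and none under sham, with no test that the two arms differ

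*Protocol article*

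**What the plan says.** All places are in the protocol article.

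- **Objective (end of Introduction).** The primary objective is to "determine whether connectivity of the cortical target for tDCS modulates responses to this intervention in people with stroke". The stated use is to select people who will respond to tDCS.
- **Role of sham (Study Design).** One of the two purposes of the sham arm is "to demonstrate that brain connectivity is not associated with response to sham tDCS".
- **Association analysis (Statistical Analysis).** "Independent variables (Textbox 5) will be correlated with the primary outcome measure for response to anodal tDCS", namely change in Fugl-Meyer upper extremity (FM-UE) score. Variables that correlate significantly go into regression models.
- **Specificity (Statistical Analysis).** Where appropriate, leave-one-out cross-validation is run in both arms "to demonstrate that the predictive model is specific to the stimulation group".
- **Between-group model (Statistical Analysis).** The only model that contains group is a "2 Group (active, sham) × 4 Time Point" repeated measures ANOVA. It has no connectivity term.
- **Intervention.** Both arms perform the same daily one-hour GRASP programme for two weeks.
- **Sample Size.** The calculation is for one correlation (r = 0.56), giving 47, raised to 68: 45 active and 23 sham, with 30% dropout allowed for.

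**The concern.** In the active arm, FM-UE change is the sum of what GRASP does and what tDCS adds. A correlation with connectivity in that arm can arise because connectivity forecasts recovery or exercise gain (a prognostic marker), because it alters the effect of tDCS (a predictive marker), or both. Only a comparison of the association between arms separates these.

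The plan has the data for that comparison but does not state it. It relies on an association in one arm and its absence in the other. Finding significance in one arm and not in the other is not a test that the arms differ, and a non-significant correlation in 16 to 23 people does not show absence. With 2:1 allocation the smaller arm is the one expected to show nothing, so the design leans towards a finding of specificity.

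At stake is the trial's main conclusion: a marker with no bearing on the tDCS effect could be put forward for selecting patients for tDCS.

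**Working it through.** **Inputs.** From Sample Size: arms of 45 and 23; 30% dropout, giving 45 × 0.7 = 31.5 and 23 × 0.7 = 16.1, taken as 32 and 16; r = 0.56; alpha 0.05, taken as two-sided because the sidedness is not stated. Assumed: the same true correlation ρ in both arms, i.e. a purely prognostic marker. The article gives no sham correlation, so ρ is varied.

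**The plan's own figure.** For one correlation, n = ((1.960 + 1.645)/atanh(r))² + 3.

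- r = 0.56: (3.605/0.633)² + 3 = 35.4, so 36, not the stated 47.
- r = 0.50: (3.605/0.549)² + 3 = 46.1, so 47.
- The inflation does reproduce: 47 × 1.12 × 1.30 = 68.4.

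The 47 therefore does not follow from its stated inputs. Nothing below depends on it; only the arm sizes, dropout and alpha are used.

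**Step 1: how often a prognostic marker looks specific.** The power of one correlation test is about Φ(atanh(ρ)·√(n − 3) − 1.96). The arms are independent, so

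P(active significant, sham not) = power(active) × [1 − power(sham)].

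Example, ρ = 0.40, arms of 32 and 16:

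- Active: 0.4236 × √29 − 1.96 = 0.32, power 0.626.
- Sham: 0.4236 × √13 − 1.96 = −0.43, power 0.333.
- Joint: 0.626 × 0.667 = 0.418.

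Simulation with t-tests of r (20,000 trials per row), with the group-by-connectivity interaction tested on the same data:

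| Arms | ρ in both arms | Active significant | Sham not significant | Both | Interaction significant |
|---|---|---|---|---|---|
| 45/23 | 0.30 | 52% | 71% | 37% | 4.7% |
| 45/23 | 0.40 | 79% | 51% | 40% | 5.2% |
| 45/23 | 0.50 | 95% | 29% | 27% | 5.3% |
| 45/23 | 0.56 | 99% | 18% | 17% | 4.9% |
| 32/16 | 0.30 | 39% | 80% | 31% | 4.9% |
| 32/16 | 0.40 | 64% | 65% | 42% | 5.1% |
| 32/16 | 0.50 | 85% | 47% | 40% | 5.0% |
| 32/16 | 0.56 | 93% | 34% | 32% | 4.9% |

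With 31 rather than 32 active completers the figures at 0.30, 0.40 and 0.56 are 30%, 41% and 32%. Outside this range the formula gives 22% at ρ = 0.20 and 3% at ρ = 0.70 (45/23), or 17% and 12% (32/16).

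**Step 2: what a null sham result shows.** If the observed sham correlation is exactly 0, the 95% interval is ± tanh(1.96/√(n − 3)):

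- n = 16: tanh(1.96/√13) = 0.50.
- n = 23: tanh(1.96/√20) = 0.41.

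With 16 participants, even a perfectly null sham estimate is compatible with correlations approaching the planning value.

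**Step 3: what a direct comparison can do.** For the difference of two Fisher z values, SE = √(1/(n₁ − 3) + 1/(n₂ − 3)). Take ρ = 0.56 under active and 0 under sham:

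- 45/23: SE = √(1/42 + 1/20) = 0.272; Φ(0.633/0.272 − 1.96) = 0.64.
- 32/16: SE = √(1/29 + 1/13) = 0.334; Φ(0.633/0.334 − 1.96) = 0.47.
- Evaluable N at 2:1: 96 (64 + 32) for 80% power, 156 (104 + 52) for 95%.

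**The case against.** **No numerical rule is written.** The article does not say that specificity means P ≤ .05 in active and P > .05 in sham. It names cross-validation, does not define specific, and does not say whether the model is refitted in sham or the active-arm model is applied there. This stands as a limit on the percentages: they describe the natural reading of Study Design, not a written criterion. It does not rescue the approach. Judging that prediction is worse in an arm half the size, with no formal contrast, has the same weakness.

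**The active-arm association is the powered analysis.** Study Design describes the primary aim in terms of the active group, and the sample size is for one correlation. That is so, but the Introduction asks about modulation, and both sections quoted above claim a contrast with sham.

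**A fuller plan may contain an interaction.** It may. The point does not rest on an omission: the article states how specificity will be shown, and that inference is unsound.

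**The rate depends on the marker.** Correct. It falls for very strong markers, because sham would then show the association too.

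**The interaction is underpowered.** Also correct. This limits what the trial can claim; it does not make the weaker rule valid.

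**Conclusion.** The concern holds. The objective is effect modification, both arms receive the exercise programme, and the stated analysis never compares the connectivity–outcome association between arms. The design could separate a predictive from a prognostic marker; the stated inference does not.

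Read as significant in active and not in sham, the approach labels a purely prognostic marker as tDCS-specific in 17% to 42% of trials for a common true correlation of 0.30 to 0.56, against about 5% for the interaction test. This assumes two-sided 0.05, equal correlations in the two arms, one connectivity measure, and arms between 45/23 and 32/16. Screening several measures is not modelled. Because the flaw bears on the primary conclusion, it should be corrected before the data are analysed.

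**What to change.** - Fit one model in all randomised participants: follow-up FM-UE on baseline FM-UE, group, connectivity and group × connectivity. Base any statement that connectivity modulates or predicts the response to tDCS on the interaction estimate and its 95% confidence interval.
- Name in advance the connectivity measure and the post-baseline visit for this model. The article lists several modalities, regions and frequency bands, and an interaction test on each would not hold 5% overall.
- Report arm-specific slopes and cross-validated prediction as descriptive.
- In Study Design and Statistical Analysis, replace the aim of showing no association under sham with estimating the difference in association between arms.

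**Cost.** The analysis text changes; no new data or participants are needed. The real price is in the claim. With 68 recruited, power for the contrast is about 47% to 64% even if the correlation is 0.56 under active and 0 under sham. These figures are for a difference of correlations and only approximate the baseline-adjusted model. Unless the sample grows towards the 96 evaluable needed for 80% power, the result should be presented as an estimate with a wide interval, not as proof of specificity.

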### Participants and Recruitment

Stroke participants will be recruited from the community by several strategies including placing information at local acute and tertiary hospitals, advertising through relevant charities and community services (eg, Stroke Foundation Australia and Stroke South Australia), speaking with local stroke survivor support groups, and advertising through social media. Textboxes 1 and 2 present the inclusion and exclusion criteria.

### Sample Size

Our primary aim is to determine the characteristics of the sensorimotor network at baseline that may predict the responsiveness to anodal tDCS in people with stroke. Therefore, our sample size calculation was based on pilot data of 10 people with stroke where we observed a medium to large effect size (r=0.56) for a correlation between baseline high beta frequency connectivity and change in cortical excitability following anodal tDCS [21]. Using this effect size with alpha set at .05 and power of 95%, we determined a total sample of 47 would be required. However, we will aim to recruit a total sample of 68, given our methodological approach of using unequal group allocation (additional 12%) and the nature of the home-based treatment with a longer follow-up study period (allowing 30% dropout). This will result in 45 participants in the active treatment group and 23 participants in the control group.

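### The requirement of 47 does not follow from r=0.56 at 95% power, and the active arm, which alone carries the primary correlation, enrols 45 and may keep about 31

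*Protocol article*

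**What the plan says.** The Sample Size section of the protocol article starts from a pilot of 10 people with stroke: "we observed a medium to large effect size (r=0.56) for a correlation between baseline high beta frequency connectivity and change in cortical excitability" after anodal stimulation. From this it concludes: "Using this effect size with alpha set at .05 and power of 95%, we determined a total sample of 47 would be required".

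Two allowances then raise the target to 68. One is 12% for allocation: "given our methodological approach of using unequal group allocation (additional 12" per cent. The other is for losses: "the nature of the home-based treatment with a longer follow-up study period (allowing 30% dropout". The section ends: "This will result in 45 participants in the active treatment group and 23 participants in the control group".

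Study Design explains the 2:1 weighting: "As our primary research aim is to investigate the brain connectivity of participants allocated to the active treatment group". Statistical Analysis correlates the baseline measures with the Fugl-Meyer change as the response to anodal stimulation. It gives the threshold as "significance level will be *P* ≤.05" without saying whether tests are one- or two-sided.

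**The concern.** Two things do not fit. First, the three stated inputs (r, alpha, power) fix the sample size for a single correlation, and the result is well below 47.

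Second, the correlation belongs to one arm, but the requirement is treated as a total and split 2:1. Sham participants cannot contribute to a correlation with response to anodal stimulation; the plan includes them partly to show that no such association exists under sham.

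This paragraph is the only justification given for the size of the primary analysis. A reader will take from it that the primary question has 47 evaluable participants and 95% power, and the design as described provides neither figure in that form.

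**Working it through.** **Inputs.** From Sample Size: r = 0.56, alpha = 0.05, power = 95%, requirement 47, allowances 12% and 30%, total 68 split 45 and 23. Sidedness is not stated, so both versions are shown.

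**1. Trying to reproduce 47.** Fisher z for one correlation: n = ((z_alpha + z_power) / atanh(r))² + 3, with atanh(0.56) = 0.633.

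- Two-sided: ((1.960 + 1.645) / 0.633)² + 3 = 35.45, so 36.
- One-sided: ((1.645 + 1.645) / 0.633)² + 3 = 30.02, so 31.
- Simulation under bivariate normality: 35 two-sided, 29 one-sided.
- Noncentral t with the predictor treated as fixed: 31 two-sided, 26 one-sided.

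None is close to 47. In the other direction, two-sided power at n = 47 is Phi(0.633 × √44 − 1.960) = 98.7%.

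**2. From 47 to 68.** Two routes reach the stated total:

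- 47 × 1.12 × 1.30 = 68.4, which uses both allowances but multiplies for dropout.
- 47 / 0.70 = 67.1, so 68, which divides for dropout but leaves out the 12%.

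Both allowances with dropout by division give 47 × 1.12 / 0.70 = 75.2, so 76.

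**3. What the active arm holds.** 68 × 2/3 = 45.3, so 45 at enrolment. After the full 30% loss, 45 × 0.70 = 31.5, taken as 31. The 47 is recovered only over both arms together: 68 × 0.70 = 47.6.

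At 2:1 an active-arm target needs a total of 1.5 times that arm, which a 12% allowance cannot supply:

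- 47 evaluable active: 47 / 0.70 = 67.1, so 68 active and 68 × 1.5 = 102 in total.
- 36 evaluable active: 36 / 0.70 = 51.4, so 52 active and 52 × 1.5 = 78 in total.

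**4. Power in the active arm.** Two-sided: Phi(atanh(r) × √(n − 3) − 1.960).

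| Active participants analysed | r = 0.56 | r = 0.50 | r = 0.40 |
|---|---|---|---|
| 31 (full 30% loss) | 91.8% | 83% | 61% |
| 45 (no loss) | 98.4% | 95% | 78% |
| 47 (as stated) | 98.7% | 95% | 80% |

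Simulation at n = 31 and r = 0.56 gives 92.5%. One-sided, Fisher z gives 95.6%. With 31, 80% power (two-sided) needs r = tanh((1.960 + 0.842) / √28) = 0.485.

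Smaller values of r deserve a place in the table because 0.56 rests on 10 people. Its approximate 95% interval, tanh(0.633 ± 1.960 / √7), runs from −0.11 to 0.88.

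**The case against.** The strongest reply is that little is lost. An over-large 47 errs on the safe side, and at the plan's own r the worst case of 31 completers is about 3 points short of 95%. This stands, and it limits the point.

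It can also be said that 95% is in fact met. The hypothesis is directional, and a one-sided test with 31 gives 95.6%. A fixed-predictor calculation gives 95.3% two-sided at 31. The first depends on a choice that the document does not state. The second suits a predictor set by design, whereas connectivity is measured. Neither brings the requirement near 47.

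Nor is 31 certain. The 30% is tied partly to the longer follow-up, and Sample Size names no time point. An analysis immediately after treatment could keep more, so 31 is the floor of a range up to 45. The two-sided requirement of 36 is met if active-arm loss is 20% or less (45 × 0.80 = 36).

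A reader might also infer how the figures arose, but the document does not settle it:

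- **Dropout wrongly multiplied by 1.30.** Division of 47 by 0.70 also reaches 68, so this is not established.
- **r = 0.50 used instead of 0.56.** Fisher z then gives 46.07, so 47. But other unstated inputs come nearly as close: a four-predictor regression test or alpha of 0.0125 gives 46.
- **The 12% as the loss of efficiency from comparing two means at 2:1** (9/8, or 12.5%). Plausible, but not stated.

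**Conclusion.** The point holds in three parts. The 47 is not reproduced from r = 0.56, alpha .05 and 95% power, which need 36 two-sided or 31 one-sided. The requirement was not carried into the arm where the primary correlation is made: that arm enrols 45 and keeps about 31 under the full planned loss. The two allowances do not together give 68 when dropout is applied by division, and 12% is not an allowance that can deliver an active-arm target at 2:1.

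The size is modest: about 92% two-sided power with 31 completers at r = 0.56, and about 98% if all 45 are kept. The margin shrinks quickly for weaker correlations. These figures assume a single correlation, bivariate normality, and that the pilot r, observed for cortical excitability, carries over to the Fugl-Meyer change.

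A reader might conclude that the trial is seriously underpowered or must recruit more. The document's own figures do not support that. What is wrong is the stated justification.

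**What to change.** Rewrite the Sample Size paragraph as follows.

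1. Present 68 (45 active, 23 sham) as the fixed size, with no forward derivation from 47. Replacing 47 by 36 and deriving forward would not restore 68: it gives 52 active and 78 in total.
2. State that the primary correlation uses the active arm only.
3. Replace the claim of 47 at 95% power by the power that the expected active completers give: with about 31, about 92% two-sided at r = 0.56 and 80% for r of 0.485 or more; with all 45 retained, about 98% at r = 0.56. State the sidedness and the assessment time point.
4. Correct 47 to 36 for the stated inputs, or give the inputs and formula that produced 47.
5. Remove the 12% allowance.

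The cost is one reworded paragraph and a slightly less favourable stated power. No participants are added, and neither the design nor the analysis changes.
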